**Research question 2 (RQ2 – effect on overall team performance)**

Do the two interventions result in a similar effect on medical students’ technical team performance (ABCDE adherence and time to critical actions)? (RQ2a)

Does VR improve overall team performance (teamwork skills, ABCDE adherence, and time to critical actions) in both intervention groups? (RQ2b)

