**Research question 3 (RQ3 – perceived effectiveness and engagement)**

Do the two interventions result in a similar engagement in VR simulation and debriefing (intrinsic motivation and perceived debriefing quality)?

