**Research question 4 (RQ4 – cognitive load)**

Do the two interventions result in a similar cognitive load?

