	**Secondary outcomes**		
	**ABCDE checklist** [46] − 20 items related to paediatric ABCDE assessment - Checklist ranges from 0 = not initiated to 3 = performed consistently during the whole simulation	RQ2: Is the change from pretest to posttest in the self-guided group comparable to that in the facilitator-guided group? RQ3: Is there a significant increase from pretest to posttest in both groups?	Mean ABCDE checklist score (mean across 20 items and across the two raters.)
	**Time to critical actions** Time (in seconds) to three predefined actions. If the team does not perform the action, they will be assigned a time of 600 seconds (maximum length of scenario).	RQ2: Is the change from pretest to posttest in the self-guided group comparable to that in the facilitator-guided group? RQ3: Is there a significant increase from pretest to posttest in both groups?	Mean time (mean across the three predefined critical actions and across the two raters.)
Individual level outcomes (n = 44 participants in each arm)	**Debriefing Assessment for Simulation in Healthcare Student Version (DASH-SV)** [47] − 6 items related to perceived effectiveness of the debriefing − 7-point Likert scale ranging from 1 = extremely ineffective to 7 = extremely effective	RQ4: Is the mean in the self-guided group comparable to that in the facilitator-guided group?	Mean DASH-SV score (mean across six items and across the three debriefings)
	**Intrinsic Motivation Inventory (IMI)** [48] − 7 items from the interest/enjoyment dimension, related to participants motivation. − 7-point Likert scale ranging from 1 = not at all true to 7 = very true	RQ4: Is the mean in the self-guided group comparable to that in the facilitator-guided group?	Mean IMI interest/enjoyment score (mean across seven items)
	**NASA Task Load Index (NASA-TLX)** [49]. - Six items related to participants perceived workload. - Scale ranging from 0 to 21. Scores are subsequently converted into a single score from 0-100.	RQ5: Is the mean in the self-guided group comparable to that in the facilitator-guided group?	Mean NASA-TLX score (mean across six items)
	**System Usability Scale (SUS)** [50] − 10 items related to perceived usability. - Likert-scale ranging from 1 = strongly disagree, 5 = strongly agree. The scores are subsequently converted into a single SUS score from 0-100 [50].	Exploratory – descriptive statistics	Mean SUS score (mean across ten items)

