### Statistical analysis

We will report descriptive statistics on baseline characteristics of each group, reporting continuous variables using median and interquartile range and categorical variables as n/total N (%). Descriptive statistics will be reported for all outcomes at each time point as mean, standard deviations, median, and interquartile range.

We will analyze the team-level data (RQ1 and RQ2) using a constrained linear mixed model with inherent baseline adjustment. Visit (pretest or posttest), assessment scenario (pneumonia or asthma), and the constrained interaction between visit and treatment group (self-guided vs facilitator-guided) will be included as fixed effects. An unstructured covariance pattern will be applied to account for the correlation between repeated measurements and potential changes in variance over time and account for missing data. The mean between the two raters will be calculated prior to statistical analysis.

To analyze individual-level outcomes (RQ3 and RQ4), we will apply a constrained linear mixed model with treatment group as fixed effect and a blocked compound symmetry pattern to account for intra-class correlation between individuals in the same team.

Missing data will be handled within the linear mixed model under the assumption that data are missing at random by including all available data points without requiring imputation. For missing individual-level covariate or questionnaire data, we will first assess the extent and pattern of missingness. If missingness exceeds a minimal threshold of >5%, we will apply multiple imputation using chained equations to account for missing values [57].

For the primary outcome (RQ1), we will report point estimates and two-sided 95% CI. Non-inferiority will be concluded, and the null hypothesis rejected, if the lower bound of the CI exceeds the negative non-inferiority margin [58,59].

For secondary outcomes (RQ2, RQ3, and RQ4), we will report point estimates, two-sided 95% CI, and p-values, and the null hypothesis will be rejected if p < 0.05. RQ5 related outcomes will be reported descriptively using median and interquartile range.

We will adjust for multiple testing using the Holm method to control the family-wise error rate within each family of research questions, except for the primary outcome [58,60].

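### RQ2a, RQ3 and RQ4 ask whether the arms are similar, but their only decision rule is a difference test at p < 0.05 without a margin, which can show a difference but never similarity

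*Protocol article*

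**What the plan says.** The Aims and research questions section words three between-arm secondary questions as questions of likeness. RQ2a, on technical team performance, begins "Do the two interventions result in a similar effect on medical" students. RQ3 asks "Do the two interventions result in a similar engagement in VR simulation and debriefing". RQ4 asks "Do the two interventions result in a similar cognitive load".

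Table 1 repeats the idea. For ABCDE score and time to critical actions it asks "Is the change from pretest to posttest in the self-guided group comparable to that in the facilitator-guided group". For DASH-SV, IMI and NASA-TLX it asks "Is the mean in the self-guided group comparable to that in the facilitator-guided group".

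The Statistical analysis section gives one rule for RQ2, RQ3 and RQ4: "we will report point estimates, two-sided 95% CI, and p-values, and the null hypothesis will be rejected if p < 0.05". It adds "We will adjust for multiple testing using the Holm method to control the family-wise error rate within each family of research questions", with the primary outcome exempt.

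The same section treats the primary outcome differently: "Non-inferiority will be concluded, and the null hypothesis rejected, if the lower bound of the CI exceeds the negative non-inferiority margin". The only margin in the protocol is the 0.5-point margin for the CTS.

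**The concern.** The question and the rule point in opposite directions. The secondary null hypothesis is not written out. Without a margin, however, a p-value on the treatment-group term tests a difference of zero. Rejecting that null shows that the arms differ. Not rejecting it shows only that the data did not settle the matter.

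What is at stake is how a non-significant result will be reported. The natural reply to a question about similarity, when p exceeds 0.05, is yes, and no sentence in the protocol stops that reply. The Pilot study section shows that the risk is realistic: it describes usability, workload and motivation as similar across the arms of a 24-participant study and mentions no margin. The Discussion expects that novices without a facilitator may miss learning points and carry a high cognitive load. An unsupported statement of similarity on ABCDE adherence or workload would therefore touch the trial's own safety-of-method question.

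**Working it through.** **Inputs from the protocol.** 22 teams and 44 participants per arm (Table 1); teams of two, randomized 1:1 (Randomization and blinding); margin 0.5, SD 0.63, one-sided alpha 0.05, power 80%, 20 teams per arm before dropout (Sample size calculation); two-sided 5% tests for RQ2 to RQ4 (Statistical analysis). The protocol gives no SD or margin for the secondary outcomes, no pretest-posttest correlation and no within-team correlation. Differences are therefore in SD units and both correlations are assumed ranges.

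**The plan's own figure.** n per arm = 2 × (1.645 + 0.842)² × (0.63 / 0.5)² = 19.6, so 20 teams. This reproduces. With the exact non-central t, 20 teams give 79.4% power and 22 give 82.8%. This is the only power figure in the protocol, and it concerns the primary outcome.

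**Team-level outcomes (RQ2a), unadjusted.**
- Standard error of the difference = √(2/22) = 0.302 SD, with 42 degrees of freedom.
- For a true difference of 0.5 SD the non-centrality is 0.5 / 0.302 = 1.66, and the probability of p ≥ 0.05 is 63%.
- The difference detectable with 80% power is 0.86 SD, and the 95% CI half-width is about 0.61 SD.
- With 20 teams per arm the 63% becomes 66%.

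**Team-level outcomes with the planned baseline adjustment.** A model that constrains the pretest means to be equal reduces the variance by about 1 − ρ², where ρ is the pretest-posttest correlation. The standard error is then √((2/22)(1 − ρ²)).

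| Assumed ρ | SE (SD) | Detectable at 80% power (SD) | Probability of p ≥ 0.05 at 0.5 SD |
|---|---|---|---|
| 0 | 0.302 | 0.86 | 63% |
| 0.3 | 0.288 | 0.82 | 60% |
| 0.5 | 0.261 | 0.75 | 54% |
| 0.7 | 0.215 | 0.62 | 38% |

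**Individual-level outcomes (RQ3, RQ4).** With teams of two the design effect is 1 + ICC, so the effective number per arm is 44 / (1 + ICC): 44 at ICC 0, 33.8 at 0.3 and 29.3 at 0.5. A true 0.5 SD difference gives p ≥ 0.05 in 36%, 47% and 53% of trials. Taking degrees of freedom from the number of teams (42) moves the ends of this range to 37% and 54%.

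**Holm.** In a family of two tests the first step uses 0.05 / 2 = 0.025. The unadjusted team-level figure then rises from 63% to 74%. In a family of one it does not change.

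**Could similarity be shown if a margin were set?** Take a true difference of zero, 22 teams per arm and no baseline adjustment. The chance that a 90% CI (two one-sided 5% tests) lies wholly inside the margin is about 5% for ±0.5 SD, 66% for ±0.79 SD (the primary ratio, 0.5 / 0.63) and 90% for ±1.0 SD; it reaches 80% near ±0.9 SD. For the 95% CI that the protocol plans to report, 80% is reached near ±1.0 SD.

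**The case against.** The strongest reply is that the harm is inferred. A reader might conclude that the plan counts a non-significant result as similarity, or counts imprecision in favour of self-guided debriefing. The text supports neither: it says when a null hypothesis is rejected and is silent on what non-rejection means. The pilot findings are labelled preliminary, and the authors concluded that a non-inferiority study could be relevant for conclusive evidence, so they did not treat the pilot as settling the question. This stands, and the point is limited to a rule that cannot answer its question.

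Estimates and two-sided 95% CIs are already promised, so readers will see the imprecision. This also stands and softens the problem, but nothing says which CI would answer the question with yes.

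A difference test has a use here. It can answer no, and the pilot did find lower perceived debriefing quality in the self-guided arm (p = 0.04). Agreed: what is missing is only the route to yes.

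A reader might also infer that Holm is the wrong method. It is sound for claims of difference. It favours apparent similarity only if non-significance is misread, and only where a family has more than one test. The family members are not listed. If each research question is a family, RQ4 has a single outcome, NASA-TLX, and Holm changes nothing there.

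Finally, margins might be in a statistical analysis plan that is not shown. But the article does state the decision rule for these questions, and that rule does not fit them. This is a mismatch in the text, not a detail left out.

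**Conclusion.** The point holds for RQ2a, RQ3, RQ4 and the corresponding rows of Table 1. The stated rule can detect a difference but cannot establish similarity, and the trial is small enough for this to matter. A moderate difference of 0.5 SD would go undetected in roughly 38% to 63% of trials for team outcomes and 36% to 53% for questionnaire outcomes. These ranges rest on assumed pretest-posttest correlations of up to 0.7, assumed within-team correlations of 0 to 0.5, and full retention of 22 teams per arm. The choice of 0.5 SD is illustrative, because the protocol does not say what difference would matter.

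It should not be read as a fault in every secondary question. RQ2b asks about improvement from pretest to posttest, which suits a difference test, and RQ5 is descriptive. The primary non-inferiority conclusion, which has its own margin and CI rule, is unaffected.

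**What to change.** 1. Reword RQ2a, RQ3 and RQ4 as estimation of the between-arm difference with its 95% CI, and change the comparability questions in Table 1 to match. Match by outcome rather than by number: Table 1 labels DASH-SV and IMI as RQ4 and NASA-TLX as RQ5, whereas the text has them under RQ3 and RQ4.
2. Add a sentence to Statistical analysis that, for these outcomes, p ≥ 0.05 is inconclusive and will not be reported as similar or comparable.
3. Keep those words only for an outcome whose CI lies wholly inside a margin that is justified and fixed before unblinding, and state the CI level used. Without baseline adjustment, team outcomes could meet only wide margins, about 0.9 to 1.0 SD, with reasonable probability; a strong pretest-posttest correlation would narrow this. Rewording is therefore the main fix.

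The cost is a change of wording in the protocol, Table 1 and any analysis plan, with no new data and no change to the model. The downside is that fewer affirmative statements of similarity will be possible. It should be done before the analysts are unblinded.

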### Ethics and dissemination

This study is approved by the Danish Data Protection Agency (Privacy, P-2023–167), and the Danish National Committee on Health Research Ethics granted an exemption from requiring ethical approval (F-23005502). The study will adhere to the Declaration of Helsinki.

Participation is voluntary, and the principal investigator will collect written informed consent and permission to record and store video data for the research project from all participants upon enrolment (see supplementary material 1.) Participants may withdraw at any time without consequence, and the intervention will be discontinued if consent is revoked. Data will be stored securely in REDCap [54], with access limited to study investigators. Video recordings are stored on secure, access-restricted institutional servers, accessible only to authorized study personnel. All recordings are used solely for blinded performance assessment and are permanently deleted after completion of the analyses in accordance with the data management plan approved by the Danish Data Protection Agency.

The trial is registered on ClinicalTrials.gov, identifier: NCT06956833, https://clinicaltrials.gov/study/NCT06956833?term=NCT06956833&rank=1 on 04/24/2025. Any protocol changes will be updated on the registry. Results from the study will be submitted to peer-reviewed open-access journals and presented at national and international conferences. Participants who request it will receive a summary of the trial findings.

## Discussion

This study is expected to provide valuable insight into the effects of self-guided versus facilitator-guided debriefing in the context of immersive VR. The findings are expected to inform the future development and integration of VR into simulation-based medical education, expanding the understanding of both the potential advantages and limitations of self-guided debriefing.

Findings from our pilot study suggest that both debriefing methods are acceptable, usable, and effective for training interprofessional teams of medical doctors and nurses in a high resource setting [30]. We will add to these findings by investigating the two debriefing approaches in a population of more novice learners. In the absence of a facilitator, learners with less developed self-regulated learning skills may struggle to frame their experiences effectively [27,61], miss critical learning points, and experience a high cognitive load [27,28].

Further, our pilot study was based on a convenience sample. This study will add to our pilot findings by applying a non-inferiority RCT design, thus enabling us to investigate whether self-guided debriefing can be considered non-inferior to facilitator-guided debriefing for improving medical students’ teamwork skills.

If self-guided debriefing proves comparably effective to facilitator-guided debriefing, it could enable greater flexibility in the timing, duration, and location of simulation-based medical education, potentially increasing access to simulation-based education in a global perspective. However, several barriers to implementing VR-based simulation remain, such as logistical, cultural, and technological barriers [11,30,44,62]. Further, this trial involves medical students in a high-income country with access to advanced technology and little is known about the feasibility and effect of VR-based simulation in low resource settings [41,63,64]. Future studies could explore the feasibility and effect of VR in other contexts, particularly those with limited access to advanced technology, technical support, or prior simulation experience, to further inform for whom and under what conditions it is most effective.

### Strengths and limitations

Key strengths of this study include its randomized controlled design and the assessment of team performance by blinded raters using video recordings of participants. Further, we will employ a broad range of validated assessment tools, professionally translated to Danish and assessed as feasible for use in a Danish context. The preceding pilot study informed recruitment strategies, intervention delivery, and assessment tool feasibility, strengthening the trial’s methodological foundation.

However, several limitations should be noted. First, the participant sample consists of medical students rather than residents or practicing clinicians, which may limit ecological validity and the direct applicability of findings to clinical practice. Second, the trial evaluates outcomes only in the short term, without long-term follow-up to assess retention of knowledge, maintenance of teamwork skills, or transfer of learning to real clinical environments. However, this design will help ensure a robust dataset with minimal missing data. Third, due to the inherent nature of comparing self-guided with facilitator-guided debriefing, participants cannot be blinded to group allocation, which may introduce performance bias. We mitigate this through standardized scenarios for both intervention delivery and performance evaluation, blinding of outcome assessors, use of validated assessment tools, and randomization to ensure balanced groups.

Fourth, randomization was performed at the team (cluster) level without stratification for potential confounding variables (e.g., prior VR or simulation experience), and team composition was not matched for, e.g., prior teamwork experience or clinical rotation level, which may introduce variability in baseline teamwork performance between groups. While baseline characteristics will be compared between groups, chance imbalances cannot be entirely excluded. Fifth, repeated testing introduces the risk of carryover or practice effects. Although scenarios differ in content but are matched for complexity, repeated exposure may lead to learning independent of the intervention. However, this is likely to affect both groups equally, potentially exaggerating overall improvements but not the primary non-inferiority comparison. Finally, although self-guided debriefing will be supported by standardized prompts to ensure consistency, there remains a possibility of variability in the depth and quality of reflection achieved between individuals and teams. These factors should be considered when interpreting the results.

## Abbreviations

ABCDE: airways, breathing, circulation, disability, and exposure
CI: confidence intervals
CTS: clinical teamwork scale
DASH-SV: debriefing assessment for simulation in healthcare student version
IMI: intrinsic motivation inventory
SUS: system usability scale
NASA-TLX: national aeronautics and space administration task load index
RQ: research question
VR: virtual reality
VRSQ: virtual reality sickness questionnaire.
